We used the Standard Protocol Items: Recommendations for Interventional Trials (SPIRIT) guideline [31] to prepare this protocol. It was peer reviewed by the Australian National Health and Medical Research Council (NHMRC) grant review panels in 2009 (GNT63329) and 2013 (GNT1071005) and by the Research Review Committee of the International Centre for Diarrheal Disease Research-Bangladesh (icddr,b). The University of Sydney Human Ethics committee and the Ethics Review Committee of ICDDR-B approved the protocols. This report combines the 2 approved protocols.

We aim to implement a community-based, cluster -randomized controlled trial to collect evidence of whether peer counseling of women to promote appropriate infant feeding can improve breastfeeding, complementary feeding, and child growth, and thus reduce the prevalence of stunting (low height-for-age) in their children up to 18 months of age. In addition, the proposed study will examine the long-term impact of peer counseling for appropriate infant feeding on child anthropometry and cognitive development at 36 and 48 months.

Our primary hypothesis is that in a community-based, cluster-randomized controlled trial of peer counseling to support infant feeding starting from the third trimester of pregnancy to 1 year after delivery will reduce the prevalence of stunting (length-for-age < –2 z score) in children at 18 months of age by 10% compared to the control group with no peer counseling.

The short-term outcomes (secondary hypotheses) are the following:

1. The percentage of children with low length-for-age, low weight-for-height, and low weight-for-age between 6 and 18 months of age will be lower in the peer counseling group than in the control group.

2. The mean length-for-age, weight-for-height, and weight-for-age in children between 6 and 18 months of age will be higher in the peer counseling group than in the control group.

3. The children's height and weight velocity from birth to 18 months of age will be higher in the peer counseling group than in the control group.

4. The percentage of women EBF (breast milk and no other foods or milk-based liquids) their infants at 3 and 6 months will be higher in the peer counseling group than in the control group.

5. The mean duration of any breastfeeding will be longer in the peer counseling group than in the control group.

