#### Infant Feeding Practices

We collected infant feeding data every month from birth to 6 months, and then at 3-month intervals between 6 and 18 months. We applied the standard Bangladesh Demographic Health Survey (DHS) questions about infant-feeding practices [37] and monitored these patterns at the 3 monthly data collection periods from birth until 18 months of age. These include questions about current breastfeeding status, current use of other liquids and solid foods, the timing of introduction of other liquids or solid foods, use of bottles for feeding, and information about who was providing advice about infant feeding among family and friends.

A senior research assistant monitored about 10% of the interviewer's scheduled visits. The supervisors checked questionnaires daily, and if the information was incomplete or not clear, they returned to the home on the next day to complete the data form. Senior research assistants verified the mother's reports of infant feeding practices through a 4-hour observation period in an unscheduled visit.

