### Schedule of Data Collection

We carried out a pilot study in the first year of the trial in a single cluster to test the recruitment methods, implementation of the intervention, the evaluation of instruments, and field methods before commencing the trial.

For the assessment of trial outcomes, we collected basic sociodemographic information about the family and maternal characteristics in a baseline survey at enrolment. We recorded the details of the birth and pregnancy shortly after delivery. We assessed the trial outcomes by measurements at monthly intervals from birth until 12 months, at 3-month intervals until 18 months, and annually until 48 months. These included anthropometric measurements, the recording of dietary patterns, dietary intake, and morbidity. The schedule of data collection is given in Figure 3.

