### Statistical Analyses

Data analysis will be by intention to treat. Analyses will be conducted at the mother-infant dyad level but will be adjusted for the community-cluster randomization [55]. The primary analyses will compare the prevalence of stunting (length-for-age < –2 *z* score) in children at 18 months of age using Pearson chi-square tests and 95% CIs for the group difference, with adjustments for clustering. We will report the results for 2-sided 5% tests.

Secondary analyses will examine each outcome variable (length-for-age, percentage EBF, duration of breastfeeding, percentage doing bottle feeding, percentage giving complementary feeds, percentage receiving diverse food groups, and mean nutrient intakes), taking account of the repeated measurements within children by using separate mixed models. We will use linear mixed models for the continuous outcomes (eg, height for age *z* score, duration of breastfeeding, Ages and Stages Questionnaire, Bayley, and Wechsler scales) and generalized linear mixed models for noncontinuous outcomes (eg, logistic mixed models for binary outcomes, such as percentage stunted or percentage exclusively breastfeeding). Models will include the treatment group as a fixed effect and infants as a random effect to account for the repeated measurements, and community cluster as a random effect to account for the cluster effect. The models will evaluate the impact of the interventions over time by testing for an interaction between time and the intervention group.

We will conduct analyses to identify the baseline characteristics of the mother-infant dyads who may benefit most from the intervention. Model assumptions will be checked, and appropriate adjustments to the analysis will be made where necessary. We will use Stata software (Stata Corp) for all analyses, with the “mixed” command to fit linear mixed models, the “melogit” command to fit mixed-effects models for binary outcomes, and the “mepoisson” command to fit mixed-effects models for event count data.

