## Results

Using satellite maps, we digitized all structures in the study areas, and from a brief census of all mapped residences, we identified a population of 65,535 people. We created a population database linked to the map structure and applied this information to define 36 clusters with 500-meter buffer zones. We randomly allocated the 36 clusters in an equal ratio to intervention or control groups but stratified by the socioeconomic status of the clusters. We screened for pregnant women in all residences and identified 5377 eligible pregnant women.

From July 2011 to May 2013, we carried out a baseline survey. In the third trimester, we examined 2050 pregnant women, including 1056 women in the intervention group and 994 women in the control group. The women participating in the trial had 1883 birth outcomes, with 993 in the intervention group and 890 in the control group. The study followed up the women who delivered the infants until 18 months of life. In December 2012, we began assessing the original cohort and completed 18 months of study follow-up in October 2014 for participants. Among them, 692 in the intervention group and 551 in the control group remained in the study until 18 months follow-up, with 301dropouts in the intervention and 339 dropouts in the control group. We continued evaluating the cohort until the children were 36 months of age, with child growth and development outcomes measured at 24 and 36 months. The long-term follow-up began in January 2015 and ended in February 2017. We have now completed the data cleaning and processing and have started analyses of the data.

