## Discussion

The 2008 Lancet Maternal and Child Undernutrition series called for high quality “how-to” research to become a priority [9,56]. It is now widely accepted that the lack of EBF and inappropriate complementary feeding are critical factors contributing to undernutrition, morbidity, and mortality in children. However, interventions to improve these critical factors have had mixed success. Ascertaining what works and what does not work is important for continuing progress on alleviating undernutrition in children. We describe the protocol and processes for implementing a randomized controlled trial in urban Dhaka, Bangladesh. The trial aims to test the efficacy of peer counseling to improve breastfeeding and complementary feeding practices and reduce undernutrition in children under 4 years of age. Breastfeeding is almost universal in Bangladesh, and the rates of EBF have increased in recent years; however, the prevalence of appropriate complementary feeding remains low. The latest available representative data (from 2017 to 2018) show that 65% of children aged under 6 months are exclusively breastfed, and only 34% of children aged 6 to 23 months are fed appropriately according to recommended infant and young child feeding practices [5,57]. Previous studies conducted in urban areas of Bangladesh using individual peer counseling have shown significant increases in EBF rates [34]. Our research will build on this work and evaluate extended peer counseling supporting both breastfeeding and complementary feeding. 

There are several limitations and challenges to the implementation of our study. One challenge will be recruiting peer counselors from a highly mobile urban mobile population and working effectively in urban slum communities. Another challenge will be training peer counselors drawn from the same disadvantaged neighborhoods to provide support to mothers and information about appropriate breastfeeding and complementary feeding. Recruiting and retaining working women with many competing demands will also be a major challenge, potentially contributing to loss to follow-up in the trial.

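### Duration of any breastfeeding, a secondary outcome, is assigned to a linear mixed model although many durations are right-censored at 18 months or at dropout, and no rule says how unfinished durations are entered

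*Protocol article*

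**What the plan says.** Secondary hypothesis 5 in the Introduction states: "The mean duration of any breastfeeding will be longer in the peer counseling group than in the control group". The Statistical Analyses section places this outcome among the continuous variables for linear mixed models ("score, duration of breastfeeding, Ages and Stages Questionnaire, Bayley, and Wechsler scales"). It describes those models as having infant and cluster random effects and a time-by-group interaction. The software is Stata, "with the “mixed” command to fit linear mixed models, the “melogit” command to fit mixed-effects models for binary outcomes", plus a Poisson command for counts; no time-to-event method is named.

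On follow-up, the Infant Feeding Practices section says: "We collected infant feeding data every month from birth to 6 months, and then at 3-month intervals between 6 and 18 months". It adds that the team "monitored these patterns at the 3 monthly data collection periods from birth until 18 months of age". The Schedule of Data Collection section is looser: it has outcomes assessed "at 3-month intervals until 18 months, and annually until 48 months" and counts dietary patterns among what was recorded.

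The Discussion remarks: "Breastfeeding is almost universal in Bangladesh". The Results section reports 993 and 890 births and 692 and 551 children at 18 months, "with 301dropouts in the intervention and 339 dropouts in the control group".

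**The concern.** A child still breastfed at the last feeding interview has a duration known only to exceed that age. This applies to every child still breastfed at 18 months and to every child lost before weaning. A linear model has no place for such a value: the age at last contact must be entered as if it were the duration, or the child must be left out. Neither recovers the mean in hypothesis 5.

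Loss also differs between arms, so some ways of entering unfinished durations produce a difference when there is none. The direction would favour the intervention, on a behaviour that it directly targets.

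A smaller point is that duration is one value per child. An infant random effect cannot be separated from the residual, and there is no time axis for the planned interaction.

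**Working it through.** **Inputs from the article.** Births 993 and 890; children at 18 months 692 and 551; 36 clusters; ICC 0.015, which the sample-size section takes from child anthropometry. **Assumed, because not given:** the share *s* still breastfed at 18 months, the timing of dropout, and the scoring rule.

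**1. Reported losses.** 993 − 692 = 301 and 890 − 551 = 339, as stated. The fractions are f_I = 301/993 = 30.3% and f_C = 339/890 = 38.1%, a gap of 7.8 points. Overall, 640/1883 = 34.0% were lost, against 22% planned.

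**2. How much is censored.** Take exponential weaning with share *s* unweaned at 18 months, and dropout spread evenly over 0–18 months and unrelated to weaning. Then

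censored share = (1 − f)·s + f·(1 − s)/(−ln s).

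- *s* = 0.5: 56.7% (intervention), 58.4% (control).
- *s* = 0.8: 82.9%, 83.7%.
- The share passes 50% at *s* = 0.43 (intervention) and 0.40 (control).

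**3. Contrast under no true effect, by scoring rule.**

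*(a) Age at last contact scored as the duration.* With λ = −ln(s)/18, a completer's mean is A = (1 − s)/λ and a dropout's mean is B = [1 − (1 − s)/(18λ)]/λ. The false difference is (f_C − f_I)(A − B).

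| *s* | A | B | False gain (months) |
|---|---|---|---|
| 0.5 | 12.98 | 7.24 | 0.45 |
| 0.8 | 16.13 | 8.37 | 0.60 |
| 0.95 | 17.55 | 8.85 | 0.68 |

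The limit is every child breastfed to 18 months, where A = 18 and B = 9. The means are 18 − 9 × 0.3031 = 15.27 and 18 − 9 × 0.3809 = 14.57, a difference of 0.70.

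For that limit, the variance is 27f + 81f(1 − f): 25.29 and 29.39. SE = √(25.29/993 + 29.39/890) = 0.242, so z = 0.70/0.242 = 2.89. With 1883/36 = 52.3 births per cluster, the design effect is 1 + 51.3 × 0.015 = 1.77, so z = 2.89/√1.77 = 2.18. It reaches 1.96 at ICC = [(2.89/1.96)² − 1]/51.3 = 0.023, and is 1.82 at 0.03 and 1.53 at 0.05.

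Other dropout timings, the same in both arms, were simulated for *s* from 0.5 to 0.95: 0.52–0.78 months for a constant hazard, and 0.90–1.25 if all dropout falls in the first 3 months.

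*(b) Weaned children only.* The false gain is 0.08–0.19 months across the simulated scenarios (about 0.16–0.17 by direct integration with evenly spread dropout). The mean then describes early weaners.

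*(c) 18-month completers, capped at 18 months.* About zero (−0.01 to 0.02 by simulation) if dropout is non-informative. This is a capped mean, and it discards the 34.0% not retained.

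**4. Censoring-aware analysis of the same simulated data.** The Kaplan–Meier restricted mean to 18 months gives −0.002, −0.016 and −0.007 months at *s* = 0.5, 0.8 and 0.9 (Monte Carlo SE 0.012, 0.009, 0.007). The plain mean gives 0.44, 0.60 and 0.65.

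**The case against.** The strongest reply is that the article fixes the model but not how an unfinished duration is derived, a detail often left to the full protocol or analysis plan. This stands in part. It rules out saying that the comparison will be biased: rule (c) leaves the group contrast near zero under non-informative dropout. It does not rescue the model, which is named outright and which, under none of the three rules, estimates the mean in hypothesis 5.

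Several stronger readings are tempting but not supported:

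- A reader might infer that control children leave earlier. The Results section gives only totals at 18 months, so they are known to leave more often, nothing more. The calculations use the same timing in both arms.
- A reader might take it as fact that most durations are censored. No share still breastfed at 18 months is given; almost universal breastfeeding makes the 40–43% threshold plausible, not certain. Nor is every lost child censored: one weaned before leaving has a complete duration. Losses may also include deaths and infants excluded after birth.
- A reader might take 0.70 months with z = 2.2 as the expected result. It is the upper end of one scoring rule with evenly spread dropout, and its significance rests on an ICC from a different outcome.

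The Schedule of Data Collection section could mean that feeding was recorded annually to 48 months. That would reduce censoring at 18 months, but not at dropout. The article also promises to check model assumptions and adjust where necessary. That leaves room for a correction but does not mention censoring, and it defers the choice until the data have been seen. The redundant infant effect would probably just be dropped and does not by itself bias the contrast.

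**Conclusion.** The point holds as a specification fault in one secondary outcome. A linear mixed model is named for a duration that is right-censored at the end of feeding follow-up and at dropout, so it does not estimate the quantity in hypothesis 5. The size of any false group difference is conditional on the scoring rule, ranging from about zero (rule c) to about 0.4–0.7 months (rule a, evenly spread dropout), and more under rule a if dropout is concentrated early. These figures assume exponential weaning, dropout unrelated to weaning, and the reported losses treated as dropout. It should be fixed, but it does not threaten the trial's main conclusion: the primary comparison of stunting at 18 months is untouched.

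**What to change.** - Analyse time to stopping any breastfeeding as right-censored data (interval-censored where only the interval between visits is known), censored at last contact. Allow for cluster by a shared frailty or cluster-robust errors, and include the socioeconomic stratum.
- Report the restricted mean to 18 months and the proportion still breastfed at 12 and 18 months, by arm.
- State the rule for children still breastfed at last contact, and for deaths and infants excluded after birth.
- Add a sensitivity analysis for informative dropout, since the survival model itself assumes non-informative censoring and the Discussion describes a highly mobile population.
- Reword hypothesis 5 to refer to time to stopping, or to the restricted mean to 18 months.
- Omit the infant random effect and the time-by-group interaction for this outcome.
- Reconcile the Infant Feeding Practices and Schedule of Data Collection sections on whether feeding was recorded after 18 months.

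The cost is one changed model and an estimand limited to 18 months. No new data are needed. The Results section says analyses have started, so the change should be dated and made before this outcome is compared between arms.

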### Identification of Clusters

The study site is a very densely populated and includes areas of slum housing where there are no established addresses and houses are very close to each other against each other along narrow paths. In this setting, there were no administrative or natural boundaries to define clusters. For the trial, we used satellite maps of the study areas in Mirpur to define clusters with buffer areas. We digitalized all structures, buildings, roads, and water bodies from satellite maps of the study area and gave each structure an identification number. Our field census team visited all the structures and buildings in the study area and identified if it was a residence or was used for other purposes. After obtaining written informed consent, we conducted a brief household census and screened for pregnant women in all residential buildings. We used the census data to create a population database linked to the mapped structures. Using geographic information system mapping techniques, we constructed 36 clusters from the population maps to cover an average population of 5000 people with a surrounding 200-meter buffer zone between clusters. We classified each cluster as low socioeconomic status or not based on the census data. Figure 2 shows a map of the study site.

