### Assignment of Treatments

We randomly allocated the 36 clusters in an equal ratio to intervention or control groups but with stratification by socioeconomic status of the clusters. We generated the random allocation sequence using SAS software (SAS Institute).

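### Clusters were randomised within two socioeconomic strata, but the primary test and the listed model terms omit the stratum, so the analysis is conservative if the strata differ in stunting

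*Protocol article*

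**What the plan says.** Under Identification of Clusters, the protocol article sets up a two-level classification: "We classified each cluster as low socioeconomic status or not based on the census data". Under Assignment of Treatments it uses that classification in the allocation: "We randomly allocated the 36 clusters in an equal ratio to intervention or control groups but with stratification by socioeconomic status of the clusters". The Abstract and the Results section repeat that allocation was stratified.

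The Statistical Analyses section first gives a general rule: "Analyses will be conducted at the mother-infant dyad level but will be adjusted for the community-cluster randomization". It then fixes the primary comparison of stunting at 18 months, "using Pearson chi-square tests and 95% CIs for the group difference, with adjustments for clustering". For the secondary analyses it lists the model terms: "Models will include the treatment group as a fixed effect and infants as a random effect to account for the repeated measurements", then "community cluster as a random effect to account for the cluster effect". Effects over time are judged by "testing for an interaction between time and the intervention group". The socioeconomic stratum appears in none of these statements. The general rule concerns correlation within clusters, not strata, and no other section brings the stratum into the analysis.

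**The concern.** Allocating "but with stratification by socioeconomic status of the clusters" balances the strata between arms, so the socioeconomic part of the between-cluster variation no longer contributes to the real sampling error of the arm difference. An analysis that ignores the stratum still counts that part as error. The estimated standard error is then too large, the interval is too wide and the test rejects too rarely under the null.

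This matters more here because the trial has less information than was planned. The sample size section assumes 50 clusters and 22% loss. The Results section reports 36 clusters, with losses of 301/993 (30%) in the intervention group and 339/890 (38%) in the control group, leaving 1243 children.

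**Working it through.** **The plan's own figure.** For 35% against 25%, two-sided 5% and 90% power, the uncorrected two-proportion formula gives 440 per arm. With the continuity correction, (440/4) × [1 + √(1 + 4/(440 × 0.10))]² = 460. Then:

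- design effect 1 + (39 − 1) × 0.015 = 1.57, and 460 × 1.57 = 722.2;
- 722.2 / 0.78 / 0.95 = 974.6, which is the stated 975 per arm.

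The planned size therefore reproduces. It takes no credit for stratification, so it is not wrong on this account.

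**Inputs for the check.** From Sampling Design and Sample Size: 35% and 25% stunted, and intracluster correlation (ICC) 0.015. From Results: 551 control and 692 intervention children at 18 months, and 36 clusters split equally (18 per arm). Assumed: *f*, the share of between-cluster variance explained by the stratum, varied from 0 to 75%; equal cluster sizes within an arm; strata evenly split between arms. The document does not give the number of clusters per stratum.

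**Standard errors.** With v = p(1 − p), each arm contributes a between-cluster part ICC × v / 18 and a within-cluster part (1 − ICC) × v / n.

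- Control: v = 0.2275; between 0.00018958, within 0.00040669.
- Intervention: v = 0.1875; between 0.00015625, within 0.00026689.
- Sums: B = 0.00034583, W = 0.00067358.

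The unstratified analysis estimates SE₀ = √(B + W) = 0.03193. Because allocation was stratified, the real standard error is SE = √(B(1 − f) + W), whether or not the stratum is modelled. At f = 50%, √(0.00017292 + 0.00067358) = 0.02909, and r = SE/SE₀ = 0.911.

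**Size and power.** The true size of the unstratified test is 2 × P(Z > 1.96/r). At f = 50%, 1.96/0.911 = 2.15, giving 3.2%. The power of the unstratified test is the chance that a noncentral t (34 df, noncentrality 0.10/SE) exceeds 2.032/r. With the stratum, it is the chance that a noncentral t (33 df, same noncentrality) exceeds 2.035.

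| f (assumed) | SE reduction | True size, unstratified | Power, unstratified | Power, stratified |
|---|---|---|---|---|
| 0% | 0% | 5.0% | 86.0% | 86.0% |
| 10% | 2% | 4.6% | 86.4% | 87.1% |
| 25% | 4% | 4.1% | 87.0% | 88.8% |
| 50% | 9% | 3.2% | 88.1% | 91.6% |
| 75% | 14% | 2.3% | 89.3% | 94.1% |

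At f = 50% the 95% half-width (1.96 × SE) falls from 6.3 to 5.7 percentage points.

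**Check by simulation.** A cluster-level analysis was simulated with 20,000 replicates, 36 clusters of 35 children and two strata of 18. At ICC 0.015 the unstratified test had size 5.0%, 4.2% and 3.2% for f = 0, 25% and 50%. Power without and with the stratum was 86.3 and 86.3%, 87.3 and 89.4%, and 88.2 and 92.0%. The small differences from the table reflect the equal cluster sizes used in the simulation.

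**Higher ICC.** With the same formulas and f = 50%, power goes from 78.2 to 86.3% at an assumed ICC of 0.03, and from 65.3 to 79.2% at 0.05.

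**The case against.** The strongest objection is that this is a condensed article, that a separate analysis plan may exist, and that stratification terms are often specified there. The list of model terms is visibly incomplete: it names an interaction with time but no main effect of time. For the mixed models this objection has some weight. It has less for the primary comparison, because the article names the test itself and a plain Pearson chi-square has no place for a stratum. Adding one would change the stated method.

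A second objection is that the size of the loss rests on an unknown. That stands. Nothing in the document says how much of the between-cluster variance a low-or-not label explains, and at 0 or 10% the gain is nil or under one power point.

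Four stronger readings are tempting, and the documents do not support them.

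- A reader might infer that the trial's result would be biased or its type I error inflated. The error runs the other way: the test is conservative.
- A reader might set the stratified power against a fixed 86% and infer gains of about 3, 5 or 8 points at 25, 50 or 75%. But stratified allocation has already reduced the real sampling error, so the unstratified test's own power also rises with f. The gains are about 2, 3.5 and 5 points.
- A reader might infer that every model gains alike. The mixed models are said to judge impact through the time-by-group interaction, which is largely a within-child contrast. In a simulated linear mixed model with 36 clusters and a strong stratum effect, adding the stratum left the interaction's standard error unchanged (0.0348 either way), while that of the arm main effect roughly halved.
- A reader might infer that a list of enrolment covariates is also needed, given enrolment after allocation and unequal dropout. That does not follow from the omitted stratum, and no calculation here supports it.

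**Conclusion.** The point holds as a modest matter of efficiency and calibration in the primary comparison. Randomisation was stratified, and the named analysis does not use the strata. At the protocol's ICC of 0.015 and the achieved numbers, the loss is between 0 and about 5 power points for a stratum share of 0 to 75%, and the nominal 5% test has a true size between 5.0% and 2.3%. A larger ICC would make the loss larger. A stratum effect is plausible, since Study Setting describes a middle-to-lower area that includes very deprived slums, but its strength is not documented. The omission and its direction are firm; the magnitude is conditional on the assumed share.

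**What to change.** Make the primary comparison a risk difference that is both stratified by cluster socioeconomic status and adjusted for clustering, or a cluster-adjusted regression with the stratum as a fixed effect. Include the stratum as a fixed effect in the mixed models too. It will sharpen the overall arm comparison there but should be expected to do little for the time-by-group interaction.

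The cost is one cluster-level degree of freedom (33 instead of 34), and no new data are needed because the classification was made before allocation. The Results section says analyses have started, so the change should be recorded with its date, before results by arm are seen if that is still possible. Otherwise both analyses should be reported.

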### Sampling Design and Sample Size

The sample size required was 1950 mother-infant dyads (975 in each treatment group) from 50 clusters with 39 mother-infant dyads per community cluster recruited over 3 months. The sample size calculation was estimated with the following assumptions: Each community cluster had an average population of 70,000 and an expected crude birth rate of 4.3 per 1000 total population over 6 months (based on the crude birth rate for urban Bangladesh of 25.8/1000 population over 36 months from the 2004 Bangladesh DHS]) thus giving an average expected number of births of 150 over 3 months per cluster. Previous research [34] indicated that appropriately 33% of pregnant women returned to their home village following delivery, leaving an expected number of eligible births of 200 over 6 months per cluster. We anticipated having 39 mother-infant dyads per cluster, assuming 95% participation but 22% loss to follow-up based on earlier research [34] from the approximately 200 mother-infant dyads available in each cluster over 6 months. We also assumed 90% power and a 5% two-sided α and intracluster correlation coefficient of 0.015 (based on analyses of the child anthropometric measurements from the 2004 Bangladesh DHS survey data for urban child populations [53]). We also expect the difference in the prevalence of stunting between the treatment groups of 10% (35% in control to 25% in the intervention group), which is similar to the change reported in an earlier education intervention for young child feeding in Peru [54]. 

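### If the secondary mixed models are run as named, arm main effects get large-sample inference although only 36 clusters carry the contrast: for linear outcomes about 6.3-6.6% type I error instead of 5% (minor)

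*Protocol article*

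**What the plan says.** All of the following is from the Methods of the protocol article.

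- **Assignment of Treatments:** "We randomly allocated the 36 clusters in an equal ratio to intervention or control groups", stratified by the socioeconomic status of the cluster.
- **Statistical Analyses, primary:** stunting at 18 months is compared by a Pearson chi-square test with a confidence interval, both adjusted for clustering. "We will report the results for 2-sided 5% tests".
- **Statistical Analyses, secondary:** linear and generalized linear mixed models have treatment as a fixed effect, infant as a random effect, and "community cluster as a random effect to account for the cluster effect". Impact over time is judged by the time-by-group interaction.
- **Software:** "We will use Stata software (Stata Corp) for all analyses", with mixed for linear models, melogit for binary outcomes and mepoisson for counts. Maximum likelihood or REML, normal or t reference, and the degrees-of-freedom method are not stated. A general sentence allows adjustments where they prove necessary.
- **Sampling Design and Sample Size:** "We also assumed 90% power and a 5% two-sided α and intracluster correlation coefficient of 0.015". This is the only ICC in the document.

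**The concern.** Treatment varies only between clusters. However many children and visits there are, a plain arm difference is estimated from 18 cluster means against 18. Two things then go wrong with large-sample inference. Maximum likelihood divides the between-cluster sum of squares by 36 rather than 34, so the standard error is too small. A normal critical value of 1.96 is also smaller than the t value on 34 degrees of freedom.

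Most secondary hypotheses are worded as arm differences in a mean or percentage. Two outcomes listed for linear mixed models have no time dimension: duration of breastfeeding is one value per child, and the Wechsler scale is given once, at 48 months. For these the arm main effect is the only available test. The error favours finding an effect and can recur across a long list of secondary outcomes.

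**Working it through.** **Inputs.** 36 clusters, 18 per arm (Assignment of Treatments). 692 + 551 = 1243 children at 18 months (Results), so 1243/36 = 34.5, taken as 35 per cluster. ICC 0.015 and two-sided 5% (Sampling Design and Sample Size; Statistical Analyses).

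**The plan's own figure.** The article gives no error rate or interval width for the mixed models. Its sample size does show which inputs were used: "35% in control to 25% in the intervention group", "assuming 95% participation but 22% loss to follow-up based on earlier research", and 39 dyads per cluster.

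- Two proportions, 90% power, with continuity correction: 460 per arm.
- Design effect 1 + (39 - 1) × 0.015 = 1.57; 460 × 1.57 = 722.2.
- 722.2 / 0.78 / 0.95 = 974.6, against the stated 975.

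So an ICC of 0.015 is the planning value. That calculation assumed "1950 mother-infant dyads (975 in each treatment group) from 50 clusters with 39 mother-infant dyads per community cluster", whereas 36 clusters were randomised.

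**Analytic size, arm main effect, 36 - 2 = 34 degrees of freedom.**

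- t critical value 2.032; 2.032/1.960 = 1.037.
- REML with a normal reference: P(|t34| > 1.960) = 0.058; interval 1 - 1/1.037 = 3.6% too narrow.
- Maximum likelihood shrinks the standard error by sqrt(34/36) = 0.972. The correct interval is 1.037/0.972 = 1.067 times as wide, so the reported one is 1 - 1/1.067 = 6.3% too narrow. Type I error is P(|t34| > 1.960 × 0.972) = 0.065.
- With a stratum term (33 degrees of freedom), maximum likelihood with a normal reference gives 7.8% too narrow and 6.9% type I error.

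**Simulation, linear model.** Null effect, 36 equal clusters of 35, no stratum, one value per child, between-cluster variance truncated at zero:

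| ICC | ML, normal | REML, normal | REML, t on 34 df |
|---|---|---|---|
| 0 | 4.5% | 4.3% | 3.6% |
| 0.005 | 5.5% | 5.1% | 4.3% |
| 0.015 | 6.3% | 5.7% | 4.8% |
| 0.03 | 6.6% | 5.9% | 5.0% |
| 0.05 | 6.6% | 5.9% | 5.0% |

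A further 200,000 simulated trials per ICC with another seed differed by at most about 0.15 percentage points. The excess fades at low ICC because the cluster variance is often estimated as zero (in 9% of maximum-likelihood fits at ICC 0.015, 37% at 0.005, 62% at 0).

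**Binary outcomes.** A logistic mixed model with Wald tests (prevalence 30%, cluster-size coefficient of variation 0.3, 1500 trials per setting, Monte Carlo standard error 0.6 points) gave 6.0% at ICC 0.015, 6.7% at 0.05 and 6.5% at 0.10. The first is (6.0 - 5.0)/0.6 = 1.7 standard errors above nominal, so on its own it is only suggestive.

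**Analyses largely unaffected.** The cluster-adjusted chi-square ran at 4.9% at the planned ICC. An approximate simulation of the arm-by-time interaction (four visits, random intercepts only) gave 5.2%, because that contrast is within children.

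**The case against.** The strongest objection is that the estimator, reference distribution and degrees-of-freedom method are details that an article commonly leaves to the analysis plan, which is not shown. The article states none of them, and its named command for linear models can itself be run with REML and a small-sample method. This stands in part: the linear figures are conditional on the commands being run without such options, and the absence of the detail is not in itself an error. What remains is that the article specifies these analyses down to the command and promises a 5% level. On the understanding that melogit and mepoisson offer only large-sample inference, the remedy for mixed has no counterpart for binary and count outcomes, and a different step has to be stated.

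Three stronger readings are tempting, and the document does not support them.

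- *The primary result is compromised.* It is not a mixed model, and the adjusted chi-square was at 4.9% at the only ICC given. Rates of 5.9-6.1% arose only at higher ICCs, which the article does not supply, and with a one-degree-of-freedom reference, which it does not specify.
- *No mixed-model outcome keeps its 5% level.* The test the article names for these models is the arm-by-time interaction, which is close to nominal under the written random-intercept model.
- *The excess is uniform.* It depends on the ICC of each outcome, and near zero the tests are conservative.

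**Conclusion.** The point holds conditionally and is minor. For arm main effects in the secondary linear models, maximum likelihood with a normal reference gives about 6.3-6.6% type I error at an ICC of 0.015 to 0.05, and intervals up to about 6% too narrow on 34 degrees of freedom. With REML and a normal reference the figures are at most about 5.9% and 3.6%. With REML and t on 34 degrees of freedom the excess is gone. For binary outcomes the direction is the same, but the size is less precisely known; no figure was computed for count outcomes.

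Assumptions: default options for the named commands, which the article does not spell out; equal cluster sizes and no stratum term in the linear simulation. The near-nominal interaction result also assumes that clusters within an arm share the same time trend. Under the same approximation a cluster-slope variance of 0.0005 (total variance 1, per visit step) raised it to 7.5%, but the document gives no basis for any such value.

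**What to change.** Add one or two sentences to the Statistical Analyses section or to the analysis plan:

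- **Linear outcomes:** fit mixed with REML and a Kenward-Roger or Satterthwaite degrees-of-freedom method.
- **Binary and count outcomes:** refer the arm effect to t with 36 minus the number of cluster-level parameters (34 with intercept and arm, 33 with the socioeconomic stratum). Alternatively, confirm it with a cluster-summary analysis or a permutation test that re-allocates clusters within strata as randomised.
- State that this applies to outcomes measured once and to arm differences at a given age.

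The article reports that analyses have started, so the choice should be recorded before arm comparisons are seen, or reported as a later clarification. No new data are needed. Intervals widen by about 4% (from REML with a normal reference) to 7% (from maximum likelihood), and the tests are slightly conservative when the ICC is near zero: 3.6% at ICC 0 and 4.3% at 0.005.
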